### Study Setting and Design

3.1

The SCOPES program will provide automated recommendations for colonoscopy surveillance intervals, which align with the timings recommended in the Australian guidelines [6], for people at elevated risk for developing CRC across five South Australian local hospital networks (inclusive of 8 hospital sites). The process will be overseen by a nurse‐coordinated team, with the digital processes streamlining existing clinical resources, using natural language processing to convert reports to structured data and provide appropriate algorithm‐based surveillance recommendations. These recommendations will be validated against existing surveillance colonoscopy data from the nurse‐led SCOOP program which has been well annotated, audited and cleaned over the years, with reviews conducted by multiple experts. These data were collected manually for a range of elevated risk indications related to personal and familial factors.

Hospital audits and patient‐reported measures will determine compliance with national guidelines for surveillance colonoscopy and consumer satisfaction before program implementation. The program will be implemented in one hospital network at a time, across five different hospital networks, and evaluated using a stepped‐wedge cluster trial design. Audits will be repeated after at least 6 months of implementation. Feasibility assessments will determine the accuracy, acceptability and cost‐effectiveness of the surveillance program compared to current practices.

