### Automated Clinical Data Collection

3.5

Relevant data (Table 2) will be sourced from each hospital's existing clinical databases. Clinical data provided in structured fields, such as in colonoscopy reports and medical records, will be cleaned and collated into relevant fields within a clinical registry in the digital platform (computer software). Relevant elements from synoptic reports and unstructured or free‐text clinical data, such as those used in histopathology and surgical reports, will be extracted and cleaned through the spaCy library in Python for natural language processing (NLP) and rule‐based regular expressions. The NLP system will account for synonyms and variations in terminology, allowing differentiation between key terms such as ‘no high‐grade dysplasia’ versus ‘high‐grade dysplasia’. The cleaned data (Table 2) will then be collated within the digital platform.

**TABLE 2 cam471456-tbl-0002:** Demographic and clinical data variables required for generating automated colonoscopy surveillance intervals.

Category	Data source	Variables collected
Demographics	Electronic medical record	Patient identifiers Age Sex Body measurements Postal address Family physician contact details Family history of colorectal cancer or genetic syndrome Personal risk factors (e.g., genetic syndromes or past colorectal cancer or neoplasia)
Colonoscopy provision	Colonoscopy reporting system	Date of procedure Proceduralist Indication for colonoscopy
Colonoscopy quality	Colonoscopy reporting system	Intubation distance Withdrawal time Bowel preparation score
Lesion detection	Colonoscopy reporting system Histopathology reports Surgery reports	Number of lesions Lesion morphology Lesion size Anatomical location Removal technique and completeness Lesion histology Presence and extent of dysplasia or invasive cancer
Other clinical factors	Electronic medical record, Colonoscopy reporting system	Comorbidities or other relevant colonoscopic observations Medications
Adverse events	Electronic medical record, Colonoscopy reporting system	Post‐polypectomy bleeding Bowel perforation Hospitalisation Death

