### Automation of Surveillance Recommendations Using Computer Algorithms

3.6

Following data collation into the clinical registry, rule‐based algorithms will provide automated recommendations for colonoscopy surveillance intervals using the patient, colonoscopy and histopathology data. Factors considered within the algorithm will include the date and quality of the colonoscopy procedure, findings from the two previous colonoscopies, age, body mass index, comorbidities that are relevant to calculating the Charlson Comorbidity Index, personal and family history of a higher risk factor including CRC, past significant neoplasia, serrated polyposis or a hereditary CRC syndrome (e.g., Lynch syndrome).

Algorithms will be primarily rule‐based, using hierarchical prioritisation. The hierarchy of criteria will be classified based on Australian clinical guidelines [6], rather than unsupervised clustering, and then integrated into recommender systems. The ruleset will be frozen, version‐controlled and include explicit conflict resolution and edge‐case handling. Risk factors considered for surveillance recommendations that align with the current Australian clinical practice guidelines are provided in Table S2.

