### Outcome Parameters

3.10

All study outcomes will be compared between baseline and post‐intervention measures. The primary outcome is the proportion of automated interval recommendations for surveillance colonoscopy that match those derived from a prespecified ruleset directly based on the Australian guidelines. This ruleset serves as the gold standard for interval assignment and is explicitly programmed from the most recent national surveillance criteria. Algorithm outputs will be independently compared against this reference ruleset, with nurse recommendations serving as a secondary comparator. Validation will be conducted blinded to algorithm outputs to avoid bias, and any discrepancies between algorithm, ruleset and clinical recommendations will be adjudicated by an independent gastroenterologist panel.

Secondary outcomes include:
The timing of the scheduled colonoscopy in relation to the recommended timeframe, with ‘on‐time’ colonoscopy defined as occurring within ±6 months of the due date specified by guideline recommendations.The time taken to review the colonoscopy outcomes and communicate the prescribed surveillance interval with the patient and family physician.The prevalence of individuals lost to follow‐up.The prevalence of patients with acceptable bowel preparation quality, complete intubation and adequate withdrawal time.The incidence rate for advanced neoplasia (with hierarchical classification prioritising invasive CRC > stage 0 CRC > advanced adenoma), including CRC, adenomatous polyps or sessile serrated lesions ≥10 mm in size, with villous change, or with high‐grade dysplasia, sessile serrated lesions with any dysplasia and any traditional serrated adenoma.The incidence rate for adverse events (e.g., bleeding, perforation, hospitalisation and death).Acceptability of the intervention to patients and clinical teams.Cost‐effectiveness of the intervention.Among the secondary outcomes, those relating to colonoscopy quality metrics and timeliness are confirmatory and prespecified, whereas patient‐reported measures and thematic feedback analyses are exploratory.

Trial findings will be reported according to the CONSORT‐AI extension guidelines [42].

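### The primary outcome scores one program of the guideline against another program of the same guideline, on inputs that the protocol does not say are independent

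*Protocol article*

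**What the plan says.** All references are to the protocol article.

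- **Primary outcome (3.10):** the "proportion of automated interval recommendations for surveillance colonoscopy that match those derived from a prespecified ruleset directly based on the Australian guidelines". The same section compares every outcome between baseline and post-intervention.
- **Reference (3.10):** "This ruleset serves as the gold standard for interval assignment and is explicitly programmed from the most recent national surveillance criteria". On the comparison: "Algorithm outputs will be independently compared against this reference ruleset", and "Validation will be conducted blinded to algorithm outputs to avoid bias". Nurse recommendations are a secondary comparator, and a gastroenterologist panel adjudicates discrepancies.
- **Algorithm (3.6):** a frozen, rule-based program. "The hierarchy of criteria will be classified based on Australian clinical guidelines".
- **Algorithm inputs (3.5):** a registry filled from structured fields and, for free-text reports such as histopathology, by natural language processing.
- **Extraction checks (3.7):** benchmarking with field-by-field reporting against the SCOOP archive, then a prospective validation at the first site.
- **Nurse step (3.8, 3.9):** a trained nurse reviews each recommendation with a checklist, and disagreements go to a third party.
- **Audit (3.1, 3.4, 3.12):** the baseline audit takes a random 10% of one year's colonoscopies per hospital from medical records. "Audits will be repeated after at least 6 months of implementation". Section 3.12 says the guideline match comes from audit data.
- **Planning values (3.11):** concordance of 60% rising to 75%.

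**The concern.** A reference standard should be able to show that the thing under test is wrong. Here the test and the reference are both programs of one guideline, and the article does not say how they differ. If both misread a rule in the same way, the episode counts as a match.

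The inputs raise a second problem. Section 3.5 gives its own example of what extraction must get right: telling the absence of high-grade dysplasia from its presence. If the reference ruleset is run on the registry, such an error feeds both programs and they still agree. A wrong interval caused by misread pathology, a main way in which a digital system can fail, would then leave the primary result untouched.

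Third, usual practice produces no automated recommendations. Read literally, the outcome has nothing to compare with in the control phase.

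**Working it through.** **1. The plan's own figure.** Inputs from 3.11: five networks, seven periods, ICC 0.01, 60% to 75%, two-sided alpha 0.05, 1417 episodes per 3-month period, power about 90%. I used the standard stepped-wedge generalised least squares variance with period effects and a random network intercept. One network crosses over per period from period 2, and cluster autocorrelation is 1, 0.8 or 0.5 (assumed).

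- With 1417 per network-period, or 1417 shared over five networks (283.4 each), normal-theory power is above 99.9%. On a t reference with 3 or 4 degrees of freedom the lowest value is 96%.
- About 90% appears only near 1417 / 35 = 40.5 episodes per network-period (91.5% to 93.8%; simulation at 40 per cell: 89.5%).

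The stated power is therefore not reproduced on the natural readings. This neither supports nor refutes the present point, but it matters for the cost of the fix.

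**2. What agreement measures.** Let c be the share of episodes in which the two programs code the rules differently, and e the share in which an extraction error changes the interval. Both are assumed, and treated as independent.

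- Reference reads the same registry data: agreement = 1 − c.
- Reference reads independently abstracted data: agreement = (1 − c)(1 − e).
- Overstatement = (1 − c) − (1 − c)(1 − e) = (1 − c)e, which is e when c = 0.

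| e (assumed) | same inputs, c = 0 | independent inputs, c = 0 | same inputs, c = 1% | independent inputs, c = 1% |
|---|---|---|---|---|
| 2% | 100% | 98% | 99% | 97.02% |
| 5% | 100% | 95% | 99% | 94.05% |
| 10% | 100% | 90% | 99% | 89.1% |
| 20% | 100% | 80% | 99% | 79.2% |
| 25% | 100% | 75% | 99% | 74.25% |

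A misreading common to both programs lowers neither column, because it is not part of c.

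**3. Does 75% fit the outcome in 3.10?** On shared inputs, 1 − c = 0.75 needs c = 25%: two programs of one guideline would differ in a quarter of episodes. On independent inputs with c = 0, 1 − e = 0.75 needs e = 25%. Neither is a natural planning value. The Introduction cites 98.7% accuracy for automated recommendations in post-polypectomy cases. The values 60% and 75% fit better as concordance of recommendations issued in practice, which is a different outcome from the one in 3.10.

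**4. What the audit sample could carry.** Suppose the audit fraction applied in every network and period. With 10% of episodes, or the 5% done for surveillance, normal-theory power by the method of step 1 is:

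| reading of 1417 | 10% audited | 5% audited |
|---|---|---|
| per network-period | 141.7 episodes: 99.9% or more | 70.85 episodes: 98.2% to 99.5% |
| total per period, shared by five | 28.34 episodes: 82.9% to 84.5% | 14.17 episodes: 58.8% to 59.2% |

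These values are optimistic for five clusters.

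**The case against.** The strongest reply is that nothing in the article says the reference ruleset reads the registry. Section 3.12 takes the guideline match from audit data, and 3.4 describes the baseline audit as a review of medical records. If audit data means manual abstraction, extraction errors would lower agreement as they should. The input source is also a detail that a condensed article may leave to a fuller document. And errors are not unexamined: nurses review every output, a nurse disagreement can reach the panel, and 3.7 tests extraction directly.

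Much of this stands. A reader might infer that agreement must be close to 100% and that the outcome cannot see extraction errors at all. The documents do not support that, because it depends on an input source they do not state. A reader might also infer that at e = 15% the whole planned 15-point effect is an artefact. That mixes two scenarios: a score of 100% against 60% is a 40-point contrast, and removing 15 points leaves 25, still above the planned 15. Nor can one say how far the between-phase contrast is biased until a control-phase value is defined.

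What does not stand is that these safeguards settle the matter. Independence and blinding in 3.10 concern outputs, not inputs. An error shared by algorithm and ruleset creates no discrepancy between them. A nurse may expose it, but is not said to work blind to the algorithm, and the nurse comparison is secondary. No rule lets a panel decision replace the ruleset result. The site-level extraction check in 3.7 is described for the first site only. Section 3.12 speaks of surveillance recommendations, where 3.10 scores automated ones.

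**Conclusion.** The point holds in three parts.

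1. **Without condition:** the primary outcome cannot reveal a misreading of the guideline shared by algorithm and reference, since both are programmed from the same source.
2. **On a condition that the article leaves open:** if the reference ruleset is applied to registry data, agreement is overstated by (1 − c)e, in practice e. That is 5 points at an assumed 5% and 10 points at an assumed 10%. The documents give no e for the trial sites. Nurse review, panel adjudication and audit data may expose some errors, but none is stated to enter the primary outcome as 3.10 defines it.
3. **On the wording alone:** automated recommendations have no control-phase value, and 60% rising to 75% does not fit algorithm-versus-ruleset agreement. Sections 3.10, 3.11 and 3.12 do not describe the same quantity.

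Because this is the primary outcome, it should be settled before rollout.

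**What to change.** Define the primary outcome as concordance of the recommendation actually issued to the patient, in both phases, with one reference interval. Obtain that interval by applying the prespecified ruleset to key variables abstracted from the source colonoscopy and pathology reports in the audit sample. The abstractor should see neither the registry fields, the algorithm output nor the issued interval.

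In addition:

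- State whether and how a panel decision replaces the ruleset result in the primary outcome. This is also the route by which a shared misreading of the guideline could be corrected.
- Reconcile 3.10, 3.11 and 3.12 so that definition, planning values and data source refer to the same quantity.
- Report algorithm versus ruleset on registry inputs as software verification only, outside the trial outcomes.

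**Cost.** A few more abstracted fields per audited record, and more than a change of wording. The primary outcome would rest on the audit sample instead of every registry episode. Audits are described only at baseline and at least 6 months after implementation, while the model has effects for seven periods, so their timing must be aligned with those periods. Power must be restated for the audited numbers: depending on how 1417 is read and which fraction counts, it runs from about 59% to over 99%.

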**Methods:**

Data from colonoscopy and pathology reports will be extracted into a clinical registry and natural language processing will be used to structure the data. Rule‐based algorithms (based on the Australian colonoscopy surveillance guidelines (but adaptable to other international standards), and with version control) will assess the need for future surveillance colonoscopies and recommend appropriate follow‐up intervals. The accuracy of the recommendations will be evaluated by nurse coordinators, with adherence to the guidelines assessed both at baseline and 6 months post‐implementation. Patient‐reported measures will be collected before and during trial implementation to assess satisfaction with the surveillance processes. Outcome measures will include evaluation of guideline compliance, key performance indicators for the quality of endoscopic services and cost‐effectiveness.

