### Validation of Digital Processes

3.7

The efficacy of data extraction, cleaning and collation, as well as algorithm accuracy will be validated in a random selection of at least 5000 archival colonoscopy reports and corresponding histopathology outcomes, which have been manually recorded as part of the long‐running SCOOP program [29], allowing testing of at least 20% of all archival data. Each colonoscopy captured as part of the SCOOP program has been manually entered into an electronic database. This manually curated SCOOP dataset will serve as the gold standard for NLP performance benchmarking. Independent assessors performing manual review will be blinded to the algorithm's output to minimise bias. All surveillance recommendations within the program have been provided by trained nurses, certified by the treating clinicians, with their accuracy audited by data scientists.

Eighty percent of the SCOOP dataset will be used for the SCOPE's digital process algorithm development and parameter tuning, and the remaining 20% will be used as a hold‐out validation dataset. Comparisons between manual and automated reporting will be performed using the SCOOP dataset as the reference standard, with adjustments made to the algorithm's parameters to ensure maximal concordance. A prospective external validation will be performed at the first implementation site prior to feedback to end users, to evaluate real‐world performance and minimise overfitting risk. Prespecified criteria for algorithm update vs. lock, including intercept/slope recalibration, will be applied while maintaining the original ruleset unchanged. All discrepancies will be manually reviewed independently by at least two team members, with the most probable reason for discrepancy identified and adjusted for algorithm improvement. Performance will be evaluated using standard NLP metrics. Precision of the digital process to measure the overall proportion of correct interval predictions will be defined as the proportion of true positive predictions; recall will gauge the model's ability to identify true positives, with the F1 score calculated to determine predictive performance. Field‐by‐field performance will be reported separately for all key variables (bowel prep quality, histology, dysplasia status and surveillance interval), distinct from overall surveillance‐interval concordance, in line with recent gastrointestinal‐specific NLP reporting standards [39].

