### Implementation of the Digital Process

3.8

This trial will compare a control phase (usual practice) with an intervention phase (the nurse‐coordinated program integrated with digital processes [i.e., SCOPES]) using a stepped‐wedge cluster trial design [40]. Implementation will commence in the second year of the study, where one new hospital network will have the intervention implemented every 6 months, until all five included South Australian hospital networks receive the intervention. The stepped‐wedge design can provide greater statistical power than a randomised parallel group cluster trial design under certain conditions, such as moderate intra‐cluster correlation (ICC), adequate cluster size and multiple steps, with fewer time constraints in the introduction of the digital processes [41]. Each hospital network is expected to perform up to 10,000 colonoscopies per year and will receive the intervention phase for at least 12 months.

Figure 1 provides an overview of the digital processes. Following the automatic upload of colonoscopy and associated pathology data into the clinical registry, the SCOPES algorithm will provide a surveillance recommendation. Each recommendation will be reviewed and approved by a trained nurse. In cases where the nurse and algorithm identify discrepant surveillance interval recommendations, conflicts will be resolved by a third‐party nurse or proceduralist as appropriate. All reasons for discrepant surveillance intervals will be recorded for quality improvement purposes.

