### Data Governance and Safety Monitoring

3.9

All study data will be stored on secure institutional servers compliant with role‐based access control, multifactor authentication and encrypted data transmission between participating sites. Automated audit logs will record all data modifications and algorithm interactions. To mitigate automation bias, nurse coordinators will review and confirm all algorithm‐generated recommendations using a structured checklist before acceptance into the patient record. A data and safety monitoring plan will oversee potential harms such as delayed colonoscopies or missed advanced neoplasia.

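### In the intervention phase nurses see the algorithm's interval before they approve it, so their approvals cannot serve as a blinded, independent comparator or as a measure of accuracy

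*Protocol article*

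**What the plan says.** All references are to the Protocol article.

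- **3.10 Outcome Parameters** makes a programmed guideline ruleset the primary reference: "This ruleset serves as the gold standard for interval assignment and is explicitly programmed from the most recent national surveillance criteria". The nurse comes second: "Algorithm outputs will be independently compared against this reference ruleset, with nurse recommendations serving as a secondary comparator". The section then says: "Validation will be conducted blinded to algorithm outputs to avoid bias". It names neither the people blinded nor the dataset. Discrepancies among algorithm, ruleset and clinical recommendations go to an independent gastroenterologist panel.
- **3.8 Implementation of the Digital Process** sets the live order: data are uploaded, the algorithm gives a recommendation, and then "Each recommendation will be reviewed and approved by a trained nurse". On disagreement, "In cases where the nurse and algorithm identify discrepant surveillance interval recommendations, conflicts will be resolved by a third" party, who may be another nurse or a proceduralist. The reasons for disagreement are recorded for quality improvement.
- **3.9 Data Governance and Safety Monitoring** says that "nurse coordinators will review and confirm all" of the algorithm's recommendations with a structured checklist, and presents this as the safeguard against automation bias.
- **Abstract, Methods** gives the nurses an evaluative role: "The accuracy of the recommendations will be evaluated by nurse coordinators".
- **3.7 Validation of Digital Processes** covers the archival SCOOP data, where "Independent assessors performing manual review will be blinded to the algorithm's output to minimise bias". It also plans a prospective external validation at the first site before results are fed back to end users.

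**The concern.** A comparator is informative only if it is formed without knowledge of what it is compared with. In the live phase the nurse starts from a displayed interval and decides whether to accept it. The recorded value is then largely an endorsement. A checklist may lessen the pull of the displayed answer, but it does not restore independence.

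If these approvals supply the nurse comparator in 3.10, or the accuracy evaluation promised in the Abstract, high agreement and a low rate of nurse correction could partly reflect the order of the workflow. The third-party step in 3.8 is triggered only when the nurse departs from the algorithm, so an interval accepted in error does not reach that step.

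This is a matter of data capture. If no interval is recorded before display, no later analysis can recover one.

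**Working it through.** The plan states no figure for nurse-algorithm agreement in the live phase, so there is nothing to reproduce. The check is a comparison of the sections, followed by an illustration on assumed values.

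**Step 1. Can the nurse be blind in each setting?**

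| Setting | Section | Nurse value formed without the output? |
|---|---|---|
| Archival SCOOP data | 3.7 | Yes: recommendations were already made by nurses and certified by clinicians; manual reviewers are blinded |
| Prospective validation, first site | 3.7 | Feasible: it precedes feedback to end users |
| Live intervention phase | 3.8, 3.9 | No: the algorithm's recommendation comes first and the nurse approves or confirms it; no pre-display entry is described |

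The blinding statement in 3.10 can be true of the first two rows but not of the third. Section 3.10 does not say which rows supply the nurse comparator. The Abstract's wording, and the opening of 3.10, which compares all outcomes between baseline and post-intervention, both lean towards including the third.

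**Step 2. Direction and bound.** Let p be the agreement between an unaided nurse and the algorithm. Let a be the share of would-be disagreements in which the nurse accepts the displayed interval. Assume that display creates no new disagreements. Then:

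- observed agreement = p + a(1 − p)
- observed discrepancy = (1 − p)(1 − a)

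Any a above 0 raises agreement and lowers the discrepancy rate. The rise is a(1 − p), which cannot exceed 1 − p.

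**Step 3. Illustration.** Both p and a are assumed. The 0.987 in the last row borrows the 98.7% that the Introduction quotes for another automated system in post-polypectomy cases. It is not an estimate of nurse-algorithm agreement in this trial.

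| Unaided p | a = 0.10 | a = 0.25 | a = 0.50 | a = 0.75 | Largest possible rise (1 − p) |
|---|---|---|---|---|---|
| 0.75 | 0.775 | 0.813 | 0.875 | 0.938 | 0.25 |
| 0.90 | 0.910 | 0.925 | 0.950 | 0.975 | 0.10 |
| 0.96 | 0.964 | 0.970 | 0.980 | 0.990 | 0.04 |
| 0.987 | 0.988 | 0.990 | 0.994 | 0.997 | 0.013 |

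Example: p = 0.90 and a = 0.50 give 0.90 + 0.50 × 0.10 = 0.95, so a 10% discrepancy rate would be recorded as 5%. At p = 0.987 the same a adds only 0.50 × 0.013 = 0.0065.

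**Step 4. What is not touched.** The primary outcome compares the algorithm with the ruleset, and the nurse's approval does not enter that comparison. A mismatch between algorithm and ruleset qualifies for the panel whether or not the nurse accepted the interval.

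**The case against.** Four points can be made for the plan.

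1. Validation is the subject of 3.7, and the blinding statement in 3.10 can be read as referring to it. A reader might infer that the stated blind is impossible throughout. The documents do not support that: both validation settings in 3.7 allow it. This stands, and it confines the point to the live phase.
2. A reader might infer that errors accepted by a nurse can never reach expert adjudication, or that the headline accuracy result is an artefact. Neither follows. Algorithm-ruleset mismatches go to the panel regardless of the nurse, and the primary outcome rests on the ruleset. The accepted errors that escape are those the ruleset comparison also misses. Nurse-algorithm agreement is also not in the list of secondary outcomes and plays no part in the power calculation.
3. The display order is inferred from text, and the workflow figure is not available here. The mention of discrepant nurse and algorithm recommendations in 3.8 leaves room for an interval formed by the nurse. Even so, 3.8 and 3.9 both describe approving or confirming an existing recommendation, and neither mentions an entry made beforehand.
4. The size is unknown. If unaided agreement is already very high, little room for inflation remains. This stands.

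None of this makes a live approval independent. Section 3.10 does not exclude such approvals from the comparator, and the Abstract points towards using them.

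**Conclusion.** The point holds for the intervention phase. Nurse approvals given after the algorithm's interval is shown cannot act as a blinded, independent secondary comparator, nor as the evaluation of accuracy. Agreement from that phase is expected to be biased upward and the discrepancy rate downward. The amount cannot be obtained from the documents and is at most 1 minus the unaided agreement.

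This rests on two assumptions: that nurses see the interval before forming their own, as 3.8 and 3.9 indicate, and that they accept at least some intervals they would otherwise have set differently. It does not extend to the primary outcome, to panel review of algorithm-ruleset mismatches, or to the two validation exercises in 3.7. The plan should be changed before the first site goes live.

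**What to change.** **In 3.10, with a matching sentence in 3.8:**

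- Restrict the nurse comparator to intervals formed without sight of the algorithm's output, namely the archival SCOOP recommendations and the prospective validation before feedback at the first site.
- Optionally add a random subset of live episodes, flagged prospectively, in which the reviewing nurse enters an interval before the platform displays the algorithm's. The existing review-and-approve step then follows unchanged. The hospital audit sample cannot serve for this, because it is drawn from colonoscopies already completed (3.4).
- State who is blinded, and to what, in each comparison.
- Report post-display agreement as an acceptance or override rate, and align the Abstract's statement on accuracy with this.

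**Cost.** Restricting the comparator and clarifying the text needs no new data, though reported agreement may be lower. The live subset needs a change of screen order and some extra nurse time. Because that time could lengthen the interval to communication, which is a secondary outcome, those episodes should be flagged or excluded in that analysis.
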